## Abstract

**Background:**

Physical activity (PA) and exercise have become an accepted and valued component of cystic fibrosis (CF) care. Regular PA and exercise can positively impact pulmonary function, improve physical fitness, and enhance health-related quality of life (HRQoL). However, motivating people to be more active is challenging. Supervised exercise programs are expensive and labour intensive, and adherence falls off significantly once supervision ends. Unsupervised or partially supervised programs are less costly and more flexible, but compliance can be more problematic. The primary objective of this study is to evaluate the effects of a partially supervised exercise intervention along with regular motivation on forced expiratory volume in 1 s (FEV_1_) at 6 months in a large international group of CF patients. Secondary endpoints include patient reported HRQoL, as well as levels of anxiety and depression, and control of blood sugar.

**Methods/design:**

It is planned that a total of 292 patients with CF 12 years and older with a FEV_1_ ≥ 35% predicted shall be randomised. Following baseline assessments (2 visits) patients are randomised into an intervention and a control group. Thereafter, they will be seen every 3 months for assessments in their centre for one year (4 follow-up visits). Along with individual counselling to increase vigorous PA by at least 3 h per week on each clinic visit, the intervention group documents daily PA and inactivity time and receives a step counter to record their progress within a web-based diary. They also receive monthly phone calls from the study staff during the first 6 months of the study. After 6 months, they continue with the step counter and web-based programme for a further 6 months. The control group receives standard care and keeps their PA level constant during the study period. Thereafter, they receive the intervention as well.

**Discussion:**

This is the first large, international multi-centre study to investigate the effects of a PA intervention in CF with motivational feedback on several health outcomes using modern technology. Should this relatively simple programme prove successful, it will be made available on a wider scale internationally.

**Trial registration:**

ClinicalTrials.gov Identifier: NCT01744561; Registration date: December 6, 2012.

## Background

Regular physical activity (PA) and exercise have become an accepted and valued part of cystic fibrosis (CF) care [1–3]. Two supervised exercise intervention studies have proven that regular vigorous exercise can positively impact forced expiratory volume in 1-s (FEV_1_) [4, 5], the single best prognostic factor for CF [6]. It has been suggested that the positive effects of regular exercise on pulmonary function might be moderated by improved airway clearance from secretions [1] and strengthening of respiratory muscles [7]. However, the exact mechanisms are unclear.

Supervised exercise interventions are expensive, not easily implemented in regular patient care and long-term adherence to supervised programs is often low [8]. In particular, long-term adherence following supervised exercise programs can be problematic [7] as such programs are often relatively monotonous and do not respond to the individual preferences of participants. Involving patients in decisions making around their exercise programs may overcome this barrier to sustainability [9, 10].

Exercise programs which are home-based and unsupervised or partially supervised have several advantages over supervised programs [7]: i) the programme can be easily implemented; ii) the patients can choose activities based on their personal preferences; iii) the accessibility of the activities with respect to location and time is much greater; iv) physical activities can be planned together with family members or friends; and v) the costs per patient and travel time commitments are much lower compared to a supervised programme. These advantages may enhance long-term positive changes in lifestyle not seen in standard supervised exercise programs [11]. Hebestreit et al., have shown that a partially supervised exercise intervention can improve forced vital capacity (FVC), exercise capacity and health-related quality of life (HRQoL) in CF [7]. Furthermore, this study demonstrated lasting benefits for these variables at 18 and 24 months after the end of the intervention [7]. If the benefits of such a partially supervised intervention can be applied to a wider population of CF patients with different health beliefs who are cared for by different health care systems, this would have significant implications for long-term outcomes in CF patients.

This randomised, parallel group study evaluates our hypothesis that a partially supervised PA programme paired with motivational feedback aimed at increasing vigorous habitual PA by at least 3 hours per week, can improve FEV_1_ and that this can be sustained over the subsequent six-month timeframe.

## Methods

### Study design

This study is an international multi-centre, randomised controlled trial with a parallel group design (Clinical trials.gov Identifier: NCT01744561). The study is conducted across CF centers in eight countries (Austria, Canada, France, Germany, Netherlands, Switzerland, United Kingdom and the United States). Patients are randomly allocated to either a partially supervised PA intervention or control intervention (no PA), see Fig. 1. Due to the nature of the intervention, blinding of participants is not possible. However, blinding of care team members and controls with respect to measurement results are done whenever possible. The study is conducted in full conformance with the principles of the “Declaration of Helsinki” (as amended in Tokyo, Venice and Hong Kong) and with the EC/ICH-Guidelines on Good Clinical Practice. The study is restricted to patients who provided written informed consent.

**Fig. 1 Fig1:**
[figure not shown]
Study design and assessment time points

### Study population

To be eligible for enrolment, patients with CF from all participating countries and centres who meet all inclusion criteria will be invited to participate in the study: i) Confirmed diagnosis of CF based on either two CF-causing mutations and/or a sweat chloride concentration during two tests of > 60 mmol/l; ii) age ≥ 12 years; iii) FEV_1_ ≥ 35% predicted [12]; iv) Access to the internet. Patients are excluded from the study if they have at least one of the following exclusion criteria: i) Participation in another clinical trial up to 4 weeks prior to the first baseline visit; ii) Status post lung transplantation; iii) Pregnancy/Breastfeeding; iv) Inability to exercise; v) More than 4 h of reported vigorous PA’s per week currently or up to 3 months prior to baseline measurements and not already planned within the coming 6 months; vi) Unstable condition affecting pulmonary function or exercise participation (i.e., major haemoptysis or pneumothorax within the last 3 months, acute exacerbation and iv-antibiotics during the last 4 weeks, unstable allergic bronchopulmonary aspergillosis, planned surgery, listed for lung transplantation, major musculoskeletal injuries such as fractures or sprains during the last 2 months, others according to the impression of the medical doctor); vii) Cardiac arrhythmias with exercise; viii) Requiring additional oxygen with exercise; ix) Recent diagnosis of diabetes 3 months prior to screening or at screening; x) Recent changes in medication 1 month prior to screening (steroids, ibuprofen, inhaled antibiotics, mannitol, DNAse, hypertonic saline); xi) At least one G551D mutation and not on ivacaftor (VX770) yet but planning to start the drug or planning to stop ivacaftor and xii) Colonisation with Burkholderia cenocepacia.

### Randomisation

Participants are randomly allocated to the intervention and control group in a one-to-one ratio using block-randomisation (block sizes of 4) and stratified by country and according to whether FEV_1_ is below or ≥70% predicted (moderate/severe lung disease vs. normal/mild lung disease) [12]. A person not involved in the study created a computer-generated randomisation list that was implemented into the database (REDCap, Research Electronic Data Capture) by a person from the Clinical Trials Unit Bern, Switzerland, offering administrative database support. Randomisation is done at each study site within the database (REDCap Software-Version 5.9.2 – © 2014 Vanderbilt University Belgium) allowing complete allocation concealment. The participant’s mean FEV_1_ value in % predicted from both baseline visits (1a and 1b) is entered and a group allocation is returned automatically. We implemented a training database with identical electronic case report forms (eCRF’s) and data collection instruments to allow study site investigators to familiarise themselves with the database before entering real patient data. The database allows entering patient data on-line from different study sites into eCRF’s. As lung function and clinical status are fundamental in this study and may change within short time periods, the intervention starts immediately after randomisation has taken place.

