### Limitations

Due to the nature of a partially supervised study, adherence to PA and data entries in the web-based diary cannot be fully controlled. However, objective measures of exercise capacity using CPET and PA (substudy using Actigraph accelerometry) will be used to verify training effects after 6 and 12-months and will provide an indication of whether study participants adhered to their training schedule or not. Blinding of study participants to minimise bias is not possible in PA intervention studies, but outcome assessors are blinded, whenever possible. A selection bias towards a physically active CF population may occur, because patients who are physically active in their daily lives might be more likely to participate in this trial.

Patient recruitment for long-term PA interventions is challenging [5], in particular in rare diseases such as CF. Moreover, there are several recent drug trials on the effects of CF transmembrane conductance regulator corrector and potentiator therapy that might interfere with the ACTIVATE-CF trial. Major efforts have been done with respect to study center recruitment. The study is currently running in > 20 specialised CF centers in eight countries in Europe and Northern America. The first study participant was enrolled in June 2014 and the last study participant is expected to complete the last study visit in June 2018.

This study could make an important contribution to the knowledge on the effects of regular vigorous PA on several important health outcomes in CF. In particular, the use of modern PA monitoring and motivational feedback embedded in the intervention will enhance our understanding on the feasibility and usefulness of these tools with respect to long-term PA adherence.

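### With one fixed block size of 4 and arms known to site staff, full allocation concealment is not assured where a team can follow its whole country-by-FEV1 stratum

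*Protocol article*

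**What the plan says.** The Randomisation section of the protocol article sets a 1:1 allocation, made "using block-randomisation (block sizes of 4"). It names no other block size. The strata combine nation and lung function, the allocation being "stratified by country and according to whether FEV_1_ is below or ≥70% predicted". An outsider to the study generated the list, and a trials-unit member loaded it into REDCap. "Randomisation is done at each study site within the database": the site enters the mean baseline FEV1 and the arm is returned. The section describes this as "allowing complete allocation concealment".

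Three other places bear on the point:
- Study design: "Due to the nature of the intervention, blinding of participants is not possible".
- Physical activity intervention, Intervention arm: the centre's own staff counsel intervention patients at the same visit, directly after randomisation, so the team knows each arm it has been given.
- Limitations: "The study is currently running in > 20 specialised CF centers in eight countries in Europe and Northern America".

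**The concern.** Holding the list in a database hides the next entry. It does not stop staff from working that entry out from earlier ones. In a 1:1 block of 4, once one arm has been used twice, the rest of the block is fixed.

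Staff who can foresee the next arm could time or withhold an enrolment, for example by bringing forward a motivated or clinically stable patient when the intervention is due. The design leaves some room for this. Eligibility is checked again at visit 1b just before allocation, the interval between visits 1a and 1b has a 7-day tolerance either way, and one exclusion rests on the physician's impression (Study population; Table 1). The resulting selection bias would work through prognosis. Adjusting for measured baseline variables would remove only part of it.

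**Working it through.** **Inputs.** Block size 4, ratio 1:1, and strata of country by two FEV1 classes (Randomisation); eight countries and more than 20 centres (Limitations); 292 patients (Sample size calculation). The article gives no predictability figure to reproduce.

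**1. Whole stratum visible, complete blocks.** There are 6 equally likely orders of two A and two B.
- Certain allocations: the fourth always, and the third when the first two match (2 of 6 orders, probability 1/3). Mean share = (0 + 0 + 1/3 + 1)/4 = 33.3%. Four orders contain one certain allocation and two contain two, so a single block can reach one half.
- Best guess: the chances of being right at positions 1 to 4 are 1/2, 2/3, 2/3 and 1. Mean = (0.500 + 0.667 + 0.667 + 1)/4 = 17/24 = 70.8%.

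**2. Average stratum.** 8 × 2 = 16 strata, and 292/16 = 18.25, so about 18 patients: four complete blocks plus two patients.
- Certain: 4 × 4/3 = 5.33; 5.33/18 = 29.6%.
- Guessed: 4 × 2.833 + 0.5 + 0.667 = 12.5; 12.5/18 = 69.4%.

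**3. Stratum shared between centres.** Strata are national and the mean is above 20/8 = 2.5 centres per country. A centre that sees only its own patients cannot tell where blocks end, so essentially none of its allocations are certain. This step is reasoning rather than simulation. The guess rate was simulated for a stratum of 18 split at random between centres, each guessing against its own running imbalance.

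| Centres sharing the stratum | Guessed correctly |
|---|---|
| 1 | 69% |
| 2 | 56% |
| 3 | 54% |
| 4 | 54% |

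**4. Varied block sizes, whole stratum of 18 visible, block ends unknown** (simulation; the observer knows which sizes are possible).

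| Sizes | Certain | Guessed correctly |
|---|---|---|
| 4 only | 30% | 69% |
| 4, 6 | 6% | 68% |
| 4, 6, 8 | 2.5% | 67% |

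**5. Illustration of bias, resting on an assumption.** Suppose staff act on every guess and shift the expected FEV1 change by +s points when they expect intervention and −s when they expect control. With guess rate g, the bias in the group difference is 2s(2g − 1). The documents give no value for s, so a range is shown.

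| s (points) | g = 70.8% | g = 56% |
|---|---|---|
| 0.5 | 0.42 | 0.12 |
| 1 | 0.83 | 0.24 |
| 2 | 1.66 | 0.48 |

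The target difference is 3 points.

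**The case against.** The strongest reply is that the decisive condition is not in the documents. Strata are by country, not by centre, and the number of centres per country is not given. Even a two-centre country does not produce certain allocations unless the sites share information. This stands, and it limits the point to teams that can follow a whole stratum.

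Second, the article prints the block size, but nothing shows that recruiting staff knew it during enrolment. The stated completion dates (June 2018 in Limitations, December 2018 in Recruitment and study procedures), with 12 months of follow-up, put the last randomisation at about mid to late 2017. Few blocks, or none, may have been unopened when the article appeared. This also stands.

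Third, varying the block size barely changes the guess rate (69% to 67%), so it does little against staff who act on probabilities. That is correct; what it removes is certainty.

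Fourth, some features make steering harder. Patients are assessed about three weeks before allocation, stratum membership near 70% is settled only at visit 1b, and eligibility and spirometry entries are monitored. These narrow the opportunity without closing it. Block size also has no bearing on effort during spirometry, so only selection is at issue here.

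A reader might go further and infer that concealment fails outright, that about 97 of the 292 allocations (292/3) were foreseeable, or that the result is biased by about 0.8 points. The documents support none of these. The list itself is hidden and no section contradicts that. The figure of 97 would need every stratum to be fully visible with complete blocks. The 0.8 points rest on an assumed shift of 1 point in fully visible strata; the same assumption gives about 0.24 points at 56% guessing.

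**Conclusion.** The point holds in a conditional form. A single fixed block size, combined with site staff who learn each arm, means the concealment claim promises more than the design secures. Where one team can follow its whole country-by-FEV1 stratum and knows or infers the block size, one third of allocations are certain on average (about 30% in a stratum of 18) and about 70% can be guessed. Elsewhere essentially none are certain and about 54–56% can be guessed. The latter figures assume that patients are split at random between centres and that centres do not share information. How many of the 292 fall in the first group cannot be determined from the article. This is a cheap improvement to the design and a correction of wording. It is not evidence that the trial's allocation was compromised.

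**What to change.** 1. For blocks not yet opened, continue the list with randomly varied sizes (for example 4, 6 and 8) within the same strata, and keep the sizes out of any document held by sites. Cost: a new list and a short amendment. The maximum imbalance within a stratum rises from 2 to 4, and the loss of power should be negligible.
2. Reword the Randomisation section so that it claims concealment of the list only, and state how many centres share each country's strata.
3. If enrolment is complete, add a check using data already collected. From the order of allocation within each stratum, compute the probability of intervention given the earlier allocations in the block (0, 1/3, 1/2, 2/3 or 1). Then examine whether baseline FEV1 and reported physical activity vary with it, allowing for stratum. Single-centre countries, if there are any, deserve a separate look. The check has limited power and covers measured variables only, but needs no change to trial conduct.

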### Withdrawal from study

The trial as a whole will be terminated prematurely if one or more serious adverse events invalidate the earlier positive benefit-risk assessment or when the time schedule cannot be met (e.g., more than doubling of recruitment time). All withdrawals are documented and the reason for withdrawal is recorded. All withdrawals will be discussed in the final report of the study. No attempt is to replace patients who withdraw from the trial.

### Physical activity intervention

#### Intervention arm

Participants in the intervention group are asked to add at least 3 hours of vigorous PA’s per week to their baseline activity. For the purposes of this study, vigorous PA is defined as activity that results in the participant breathing rapidly, only able to speak in short phrases, where heart rate is increased substantially, and sweating is present [13]. Including the activities already present at the baseline assessment, this should include at least 30 min of strength building exercises and 2 hours of aerobic PA’s per week. The remaining time can be attributed according to the participant‘s preferences. PA bouts lasting 20 min or longer will be counted with respect to total weekly training time.

At the second baseline visit, following randomisation, the participants in the intervention group will undergo an assessment of their preferences and motivation, followed by counselling immediately and at all subsequent study visits scheduled every 3 months. The counselling and activity assessments are done in each centre by a designated team member (physiotherapist or exercise specialist) who receives prior training so that a standardised approach is ensured. The participants complete a self-administered activity questionnaire and a structured interview using a standardised motivational interview form is carried out to assess the participant’s likes and dislikes with respect to PA’s and to identify possible barriers and determine the motivation (using a 10-point Likert Scale) of the participant to start specific activities and to make individualised PA recommendations. Based on the information from the questionnaire and interview, the physiotherapist/exercise specialist and the participant/his guardians engage in a dialogue identifying additional PA’s that are strength building and/or promoting aerobic fitness that will result in an additional 3 h per week of these activities at a vigorous level. Participants of the intervention group are also told a target heart rate range corresponding to 60–80% of peak oxygen uptake (VO_2peak_) for vigorous continuous aerobic type activities [13]. VO_2peak_ is determined during incremental exercise tests at baseline and after 6 months. Patients also receive training how to determine heart rate during exercise.

Participants receive further motivation by being equipped with a three-axial pedometer (Omron HJ-322 U-E). Participants are instructed to wear the pedometer on a daily basis and they are asked to complete a web-based log (http://www.activate-cf.org/) on a daily basis. The user interface of the website is programmed to allow access from classical personal computers, palm tops, tablets and smartphones. Participants are asked to document daily steps from their pedometer and training activities in their web-based logbook, using an individual pseudonym login that is provided by their study centre. In the web-based log book, data on i) vigorous PA’s performed that day (type of PA, duration), ii) total daily step count and exercise step count (steps with estimated energy expenditure of at least 3 metabolic exchange units-METS), and iii) time in sedentary activities (i.e. watching TV, playing video games without activity components, computer time, driving, taking a nap/sleeping) are entered.

The central monitoring unit in Wuerzburg, Germany is responsible for monitoring data entries on the web-based log. The participant’s CF centre will be notified if there have been no completed entries into the system for the previous 3 days or longer. The participants receive a “reminder” message on his or her mobile phone or via email if no entries have been made for three consecutive days. If there are no entries for a whole week, participants are contacted by phone from their centre’s designated activity contact person (i.e., physiotherapist, exercise specialist).

Participants complete a PA questionnaire at all clinic visits. The web-based training logs are checked at the clinic visits and discussed with the participant by the physiotherapists/exercise specialist. The physiotherapist/exercise specialist utilises this information, along with the web-based logs and the interview to provide exercise counselling at every visit to the centre. If necessary, a new activity plan will be created.

There are scheduled phone contacts after 1, 2, 4 and 5 months by the physiotherapist/exercise specialist into the training to discuss progress and to re-counsel the participants PA plan. During the monthly scheduled telephone contacts, the participant is asked about his or her weekly exercise activities and the written activity agreement is reviewed. Likewise, the web-based activity log is discussed with the participant. If one or more goals of the plan have not been met or problems have been encountered or new activity ideas come up, the plan is modified. The structured interview forms available for the initial counselling are used to assist as needed. In case of admission to the hospital, physical exercise is included in the in-patient treatment (the treating physician needs to decide what is possible).

After the six-month assessment, participants of the intervention group will keep their pedometers and still have access to the web-system to report and view their PA data. Centre staff meets with participants as part of routine care and as deemed necessary by the treating physician. Staff members do not receive the data collected, unless clinically relevant, such as a change in glycaemic control, and advise the patient based on the information that they gather from the patient.

